**Methods:**

This randomised controlled trial will evaluate the effectiveness of an education program on knowledge, self-care and health-related quality of life of Thai HF patients and their carers. Assessments will be conducted at baseline, three and six months. Participants will be assigned by independent random allocation to an intervention (family-based education plus usual care) or a control (usual care) group. Analyses will be conducted on an intention-to-treat basis.

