### Participant eligibility

Participants for this study will be a dyad consisting of a patient and their partner or family member that is identified as providing informal care. All participants will need to have sufficient comprehension to read Thai without the need for a translator. The patients will be aged 20 years or over, although with the increasing prevalence of HF in the elderly, it is envisaged that the majority will be above 50 years of age. The inclusion criteria for HF patients are: 1) a primary diagnosis of HF NYHA (New York Heart Association) class I to III confirmed by the treating doctor and determined by a history of typical signs and symptoms and physical examination [45] and, where possible, objective evidence of cardiac dysfunction on echocardiogram; 2) at least one family member residing with them; 3) contactable by telephone at home; and 4) a DVD player at home. The inclusion criteria for carers are: 1) living in the same household as the HF patient or someone of the patient’s own choice; and 2) aged 20 years or over. Participants will be excluded if they reside in an urban area, have a documented history of dementia or severe psychiatric illness, are unable to continue to follow the protocol, and have severe symptoms indicative of acute heart failure [24, 46] or complications from cardiac or disease or other life threatening comorbidities.

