#### Data analyses and sample size calculation

Data collected will be entered into the Statistical Package for the Social Sciences (SPSS Inc.). Descriptive statistics will be used to analyse demographic data. The sample size calculation is based on changes in HF knowledge. In a previous study investigating HF knowledge as the primary outcome [22]), a sample size of 50 per group and allowing for a 10% attrition rate, had adequate power (0.80) with a two-sided 95% significance to detect a difference of two-points on the DHFKS between the intervention and control conditions in mean post-test versus pre-test changes on the DHFKS and 93% power to detect clinically significant difference in MLHF scores of 6-points. For this study, assuming a medium effect size (0.65) in the between-group differences on the DHFKS and allowing for a 20% attrition rate, the minimal sample size of 40 per group will have sufficient power (0.80). An independent t-test will be used to test the overall differences of the DFHKS, SCHFI, CAS, MLHF and SF-12 within the groups and between the control group and the intervention group at baseline and over three and six months. Two-way repeated measures analysis of variance (ANOVA) will be used to test the difference between groups and change overtime in each group of the main outcomes (DFHKS, SCHFI, CAS, MLHF and SF-12). Treatment failure and withdrawal will be considered on an intention-to-treat basis, with the aim of providing a more realistic estimate of the difference between the two groups.

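### Intention-to-treat is promised, but the repeated-measures ANOVA named to deliver it is, without imputation, a complete-case analysis

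*Protocol article*

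**What the plan says.** The article commits to intention-to-treat twice. The abstract says "Analyses will be conducted on an intention-to-treat basis", and the section on data analyses and sample size says "Treatment failure and withdrawal will be considered on an intention-to-treat basis".

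The same section names two methods for all outcome scales. The first is a t-test: "An independent t-test will be used to test the overall differences of the DFHKS, SCHFI, CAS, MLHF and SF-12", between arms at baseline, three and six months. The second is longitudinal: "Two-way repeated measures analysis of variance (ANOVA) will be used to test the difference between groups and change overtime in each group". The software is SPSS, and the abstract gives the schedule: "Assessments will be conducted at baseline, three and six months". The section names no imputation, mixed model or other device that would bring a person with a missing visit into the ANOVA.

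The sample size rests on "assuming a medium effect size (0.65) in the between-group differences on the DHFKS", 20% attrition, power 0.80 and a minimum of 40 per group. Recruitment sets at least 100 dyads, and Randomisation sets a 1:1 ratio.

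Among the exclusions, Participant eligibility lists people who "are unable to continue to follow the protocol".

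**The concern.** A standard repeated-measures ANOVA needs a full set of scores for each person. Someone assessed at baseline and month 3 but not at month 6 contributes nothing to it, although two of three scores are in hand. Intention-to-treat asks that everyone randomised be analysed in the allocated arm. The article states both the principle and the method, and without a further step the method does not deliver the principle.

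Two things are at stake. If dropout is related to knowledge, health or engagement, and that relation differs between arms, the comparison among people with complete data no longer has the protection of randomisation. And the result would be reported as intention-to-treat when the analysed set is something else. This touches both primary outcomes, the patients' knowledge score and the carers' perceived-control score.

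**Working it through.** **1. Reproduce the sample size.** Inputs from the analysis section: standardised effect 0.65, power 0.80, 20% attrition. Two-sided alpha of 0.05 is stated there only for the previous study and is assumed to carry over.

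- Normal approximation: n = 2 × (1.960 + 0.842)² / 0.65² = 37.2, so 38 per group. The exact noncentral t gives 39.
- Inflated for 20% attrition: 38 / 0.8 = 47.5, so 48; 39 / 0.8 = 48.75, so 49.
- 100 dyads at 1:1 is 50 per group, and 50 × 0.8 = 40.

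The stated 40 therefore reproduces as the number analysed after attrition. Read as the number enrolled it does not: 40 × 0.8 = 32, with power of 72.6%. The power statement thus counts on about 80 analysed dyads of 100 randomised.

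**2. What complete-case analysis costs in power.** Exact t, effect 0.65, a two-group comparison rather than the ANOVA's own test:

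| Analysed per group | Power |
|---|---|
| 50 (all randomised) | 89.6% |
| 40 (after 20% loss) | 81.9% |
| 32 | 72.6% |

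The planned 80% survives if 20% is the total share with any missing visit. The ANOVA needs every visit, so scattered misses add up. As an illustration, if each follow-up visit were missed independently by 10%, 50 × 0.9² = 40.5 per group would be complete; at 20% per visit, 50 × 0.8² = 32.

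**3. What it could do to the estimate.** The document gives no dropout pattern, so this part is assumption. Take scores with SD 1, a true effect of 0.65 at months 3 and 6, and 20% dropout after month 3. In the selective arm, let dropout fall at random on half of the lowest 40% of month-3 scorers. The mean of the lowest 40% of a normal distribution is −0.386 / 0.4 = −0.966 SD, so the remaining 80% shift upwards by 0.2 × 0.966 / 0.8 = 0.241 SD at month 3. At another visit the shift is 0.241 times that visit's correlation with month 3. With correlations of 0.5 to 0.7:

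| Selective dropout in | Six-month score difference | Month-3 change difference |
|---|---|---|
| Intervention arm only (control random) | 0.65 + 0.12 to 0.17 = 0.77 to 0.82 | 0.72 to 0.77 |
| Both arms alike | 0.65 | 0.65 |
| Control arm only (intervention random) | 0.65 − 0.12 to 0.17 = 0.48 to 0.53 | 0.53 to 0.58 |

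The month-6 change difference is biased by 0.241 × (correlation of months 3 and 6 − correlation of baseline and month 3). That is zero when the two correlations are equal. At 0.7 and 0.5 it is 0.048, giving 0.70 or 0.60 according to the arm. A likelihood estimate using all observed scores returns 0.65 throughout, because dropout here depends only on an observed score.

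**4. The t-tests.** In this scenario everyone is seen at month 3, so the month-3 t-test gives 0.65. The month-6 t-test still omits everyone lost by month 6 and carries the six-month column above.

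**The case against.** The strongest reply is that a completers analysis is never stated. The article says that withdrawal will be handled by intention-to-treat, an ANOVA on imputed data would be consistent with that, and missing-data detail is often left to a fuller protocol or analysis plan that is not shown. This stands as far as it goes: the point is not that an imputation paragraph is absent, but that the stated method needs one to match the stated principle, and that a better method is available in the same software.

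A reader might infer that the result will be biased in favour of the programme. The document does not support this. That direction needs selective dropout in the intervention arm only; similar dropout in both arms gives no bias, and control-only dropout reverses it. Controls receive matched telephone calls, and outcomes may be collected by telephone, both of which weaken the case for differential loss. The sample size is based on change in knowledge, and the month-6 change contrast is little affected or unaffected under these assumptions.

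A reader might also infer from "are unable to continue to follow the protocol" that randomised dyads will be removed for non-adherence. The phrase stands in a list of screening conditions such as urban residence and dementia. Staff can judge at screening whether a dyad could keep to the schedule, and nothing in the article applies the criterion after randomisation. What remains is loose wording.

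Finally, the t-tests do retain month-3 data, and the planned numbers absorb a 20% loss. Both are correct.

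**Conclusion.** The concern holds in limited form. As specified and without imputation, the repeated-measures ANOVA analyses only people with all three assessments: about 80 of 100 randomised dyads at the planned attrition. That does not match an intention-to-treat label. Power is not the main harm (about 82% against about 90%, assuming two-sided 5% and 20% total incompleteness). The harm is possible selection bias. Its direction and size cannot be derived from the document, and the illustrative figures depend wholly on an assumed dropout pattern. The t-tests relieve the problem at month 3 but not at month 6. The eligibility phrase is a minor wording matter. Severity: should-fix.

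**What to change.** - Replace the two-way repeated-measures ANOVA with a linear mixed model for repeated measures (SPSS MIXED) for each outcome: visit, arm, arm-by-visit and unstructured covariance. Include all randomised dyads in their allocated arm and every available score.
- Keep baseline in the outcome vector, or state how dyads with no follow-up score are handled. A model that uses baseline only as a covariate would drop them again.
- Add a prespecified sensitivity analysis for missing data. If the ANOVA is kept, prespecified multiple imputation is the alternative route to the same end.
- State that dyads who stop the programme or the calls are still assessed at three and six months.
- Limit the inability-to-continue exclusion in Participant eligibility explicitly to screening before randomisation.

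The cost is slightly more analysis work, some effort to follow dyads who stop, and reliance on a missing-at-random assumption, which the sensitivity analysis should probe. The software, visits and sample size do not change.

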#### Process evaluation

Ongoing monitoring of program activity in both the intervention and control group will be regularly conducted. Participants will be interviewed when the principal investigator performs a telephone follow-up. Participants in the control group will be asked how satisfied they are with regular telephone contact. The investigator will pilot test the DVD and HF manual in six HF patients and carers prior to implementation of intervention, to ensure their usability and refine if necessary. Participants in the intervention group will be asked how satisfied they are with the DVD and the HF manual and telephone follow-up. At the end of the program participant satisfaction will be measured using a visual analogue scale and participants will be invited to offer additional comments. Completion of activities in the HF manual will be assessed by viewing participants’ HF manual at the six-month assessment. This process assessment is integral to identifying cultural and social facilitators of, and barriers to, the process of lifestyle behaviour change to improve HF risk as a result of this educational intervention.

## Discussion

This trial will test the effectiveness of a family-based education program for HF patients and their carers residing in rural Thailand. Patient education is rapidly becoming recognised as a key component of HF management. Unfortunately, most trials of such programs have been undertaken in Western countries which have considerable differences to Asian countries in terms of, for example, patient characteristics, settings, interventions, and outcome measures. This is the first trial of such a program in rural Thailand taking into account cultural and societal factors.

The trial will not only provide evidence pertaining to the effectiveness of education programs for Thai HF patients, but it will be the first to include family members. We hypothesise that a family-based education program will improve HF knowledge, self-care and HRQoL in patients and carers in rural Thailand. This will be assessed via the implementation of a HF manual and DVD specifically developed to meet the knowledge requirement of HF patients and carers.

## Abbreviations

HF: Heart Failure
Thai ADHERE: Thai Acute Decompensated HEart Failure REgistry
HRQoL: Health-Related Quality of Life
CONSORT: Consolidated Standards of Reporting Trials
NYHA: New York Heart Association
DVD: Digital Video Disc
DHFKS: Dutch Heart Failure Knowledge Scale
CAS: Control Attitudes Scale
SCHFI: Self-Care of HF Index
MLHF: Minnesota Living with Heart Failure questionnaire
SF-12: Short-Form 12-item health survey
ANOVA: ANalysis Of VAriance.
